### Statistical analysis

Demographic and baseline data will be fully described and all outcome data will be analysed and reported. Significance will be assumed to be 5% throughout, and 95% confidence intervals will be quoted. All data will be anonymised and coded so that data collection and statistical analysis are blind to treatment allocation. The code will be broken only after the primary analysis has been completed. A fully pre-specified analysis plan will be prepared prior to the data being released to analysts. The analysis will be performed on a “Treatment as Allocated” principle to ensure protection against unintended bias. The data will be fully imputed in line with the pre-defined statistical analysis plan to minimise data loss due to missing values or time points. Sensitivity analyses (best case/worst case) will be performed to assess the influence of differing imputation assumptions. All trial reporting will be CONSORT-compliant
[77].

For each outcome measure, at both post-intervention and follow-up, three analyses will be presented, the first two being unadjusted and adjusted treatment-as-allocated analyses and the third a treatment received analysis:

1. An unadjusted two-sample *t*-test by allocation group.

2. An analysis of covariance with baseline score and stratification variables as the covariates and allocated group as the condition factor. Between-group effect sizes with confidence intervals will be calculated using Cohen’s d. Centre will be added as a fixed factor to test and quantify any site-specific effects, and if the number of practitioners is greater than the number of centres, practitioner will be added as a random factor.

3. A repeat of analysis 2 with treatment compliance factored in.

If CR is shown to be effective, additional forward stepping regression modelling will be undertaken to identify factors important in maximising the observed effects. Factors that will be investigated will include diagnostic category, medication status, educational level, social class, caregiver relationship to the person with dementia (spouse, adult child, other), and whether or not the carer is residing with the person with dementia.

For the cost-effectiveness analysis (CEA), service utilisation and carer input data will be collected using the CSRI. Unit costs will be attached to service use measures (from national reference costs, the PSSRU compendium
[78] or calculated anew), CR costed in liaison with providers, and carer inputs valued using opportunity and replacement cost options. The CEA will look at changes over 9 months from each of two perspectives (health and social care; societal) in four analyses: cost of achieving an incremental change in BGSI; cost of achieving incremental changes in self-efficacy for participants with dementia; cost of achieving incremental QALY gains for participants with dementia; cost of achieving incremental QALY gains for carers. Incremental cost-effectiveness ratios will be computed as required and acceptability curves plotted for a range of willingness-to-pay values. Net-benefit regressions will make it possible to control for site, baseline outcome measures (where appropriate) and baseline costs, as well as gender, age and MMSE score. Sensitivity analyses will be conducted to test for different assumptions in the attachment of costs. We will also estimate the investment costs and net costs to the NHS and the social care system of making CR available nationally.

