### The cognitive rehabilitation intervention

CR is an individualised approach for people with dementia (PwD) aimed at managing or reducing functional disability and maximising engagement and social participation. PwD and their carers work together with a health professional over a number of sessions to identify personally relevant goals and devise and implement strategies for achieving these. CR will be delivered in ten individual sessions over 3 months, followed by four maintenance sessions over 6 months. Carers will be involved in part of each session where possible. Involvement of a carer helps to ensure that skills are maintained and applied to novel situations and facilitates communication about how current or possible future difficulties might be managed.

Over the course of the 10 weekly sessions, participants with dementia will work in collaboration with the therapist to address personal rehabilitation goals. Drawing on the goals identified at baseline assessment, up to three behavioural goals will be operationalised, and strategies for addressing these will be devised and implemented. Goals will be introduced one at a time, in a flexible manner depending on rate of progress. Following introduction and modelling of strategies and skills during the therapy sessions, the participant and carer will work on the selected goal between sessions following an agreed schedule of activities. Progress with each goal will be reviewed and the strategies adopted will be adjusted as necessary on a weekly basis. Performance for each goal will be independently rated at the outset and in week 10 by the participant, carer and therapist, and the therapist will rate the extent of goal attainment following the sessions in week 10. Work on goals will be supplemented by the following components, designed to support the ability to make progress with the selected goals and address barriers to progress, which will be systematically introduced across the ten sessions:

1. Introduction of, and practice in applying, a solution-focused problem-solving approach by following a short sequence of steps to specify and test possible solutions.

2. Introduction of anxiety management strategies, building on participants’ existing strengths and preferences in this area, and practice in strategy use and application.

3. Monitoring of activity levels, leading to plans for increasing engagement in meaningful and enjoyable activity, and implementation of these plans.

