4. Practice in strategies for maintaining or improving attention and concentration.

5. A review of compensatory strategy use (e.g. calendars, diaries, reminder systems) and development and implementation of plans for improving strategy use, which might include increasing the efficiency of existing strategies and introduction of new strategies.

6. A review of current use of restorative strategies for retaining new information or improving recall, and practice in key strategies (mnemonics, semantic association, spaced retrieval), enabling participants to identify a preferred strategy and apply this in everyday situations.

In addition, to ensure sensitivity to the wider context, where appropriate a discussion of carer well-being and strategies for managing stress will be initiated, and information will be provided about additional sources of support and help, with encouragement to access these. The four maintenance sessions will focus on supporting maintenance of gains and encouraging continued goal performance and strategy use. The therapist will re-rate the extent of goal attainment following the session in week 14.

The effects of the CR intervention will be compared to treatment as usual (TAU). In the pilot, CR was compared with TAU and with an attention placebo condition (relaxation therapy). There was no evidence of a difference between the two control groups, which suggests that TAU can serve as an appropriate comparator. For the CR group, the CR will be provided in addition to TAU, while the control group will receive only TAU and will have no contact with the research team between assessments. TAU will consist of acetylcholinesterase-inhibiting medication where prescribed, and any other services normally provided apart from specific programmes of cognitive rehabilitation or other cognition-focused intervention. TAU may include, for example, routine monitoring by the Memory Clinic, information provision, attendance at drop-in groups or support groups, or carer participation in support groups. Service receipt during the intervention period, including dementia-specific services, monitoring and interventions provided by Memory Clinics, will be documented for all participants. All participants will be free to access services such as those offered by the Alzheimer’s Society, and the extent of this will be recorded.

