#### (8) Treatment compliance

Treatment compliance will be indexed by the number of sessions completed for each participant.

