Other protection from bias will include the method of allocation to groups. The randomisation will be performed independently of the data analysis team by the CTU using a dynamic, stratified, web-based system designed to protect from bias by the unpredictability of the algorithm and the security of the web-based programme. Blinding will be maintained by automatic generation of randomisation codes and distribution via e-mail directly to the therapists responsible for implementing the treatment. Further bias protection will come from a “treatment as allocated” analysis, which will be the principal analysis performed on both primary and secondary outcomes. Treatment compliance measures will be restricted to inclusion in secondary analyses.

We will collect basic anonymised demographic data and reasons for not progressing to trial participation for all those people identified as warranting screening and invitation to the trial but declining to be screened or to participate. These data will be reported on a CONSORT diagram, together with information on the amount and nature of missing data, to enable readers to assess bias arising from recruitment or acceptability issues within the trial.

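### The secondary treatment-received analysis conditions on sessions attended, which only CR participants can have, so it does not yield a randomisation-protected effect of treatment received

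*Protocol article*

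**What the plan says.** Under Statistical analysis, three analyses are to be presented for each outcome, at post-intervention and at follow-up. Two are as-allocated, and "the third a treatment received analysis". Analysis 2 is "An analysis of covariance with baseline score and stratification variables as the covariates and allocated group as the condition factor". Analysis 3 is "A repeat of analysis 2 with treatment compliance factored in".

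The compliance measure is defined under Outcome measures, item 8: "Treatment compliance will be indexed by the number of sessions completed for each participant". On what each arm can receive, the section on the intervention says "CR will be delivered in ten individual sessions over 3 months, followed by four maintenance sessions over 6 months", whereas "the control group will receive only TAU and will have no contact with the research team between assessments". Under Procedure, the maintenance sessions come after the post-intervention assessment, the treatment-as-allocated analysis is the principal one, and "Treatment compliance measures will be restricted to inclusion in secondary analyses".

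**The concern.** The session count is a post-randomisation variable that can differ from zero in one arm only. Within CR, nobody is randomised to attend more or less. People who attend less may differ in health or engagement from those who attend fully, and TAU has no observed counterpart to them. A regression that conditions on the count therefore mixes the effect of therapy with whatever drives attendance.

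The document makes such a link plausible. The pilot's discontinuations (Background) include physical illness, death and self-withdrawal, and Ethical considerations stresses that the therapy depends on active engagement.

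At stake is how a result labelled as treatment received is read when it is printed beside the two as-allocated results for each outcome. A null or negative arm coefficient could be taken as evidence against CR, and a session slope produced by selection could be taken as dose-response.

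**Working it through.** **Inputs from the article.** Form of analyses 2 and 3, and compliance as sessions completed: quoted above. Possible sessions: 10 before the post-intervention assessment, 10 + 4 = 14 before follow-up, 0 in TAU. Sample size section: effect 0.3, alpha 0.05, power 80%, 175 completers per arm, 27% attrition, 480 randomised. Allocation 1:1.

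**Inputs assumed, not in the article.** Mean and SD of sessions in CR, the link between attendance and prognosis, and a two-sided alpha.

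**1. The plan's own figure.** n per arm = 2(1.960 + 0.842)²/0.3² = 2 × 7.85/0.09 = 174.4, so 175. Total = 350/0.73 = 479.5, so 480. Both reproduce. The article gives no figure for analysis 3.

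**2. Sessions added to arm: collinearity.** If every CR participant attends the same number, the columns (intercept, arm, sessions) have rank 2 of 3 and aliasing is exact. Otherwise, with equal arms and CR mean m and SD s, the squared correlation of arm with sessions is m²/(m² + 2s²), so

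VIF = 1 + m²/(2s²).

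| Assumed m / s | VIF | SE multiplier (√VIF) |
|---|---|---|
| 13 / 1 | 1 + 169/2 = 85.5 | 9.2 |
| 12 / 2 | 1 + 144/8 = 19.0 | 4.4 |
| 11 / 3 | 1 + 121/18 = 7.7 | 2.8 |
| 10 / 4 | 1 + 100/32 = 4.1 | 2.0 |

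Only the ratio m/s matters. At post-intervention, where at most 10 sessions are possible, 9/1.5 also gives 19.0.

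**3. What the coefficients mean.** TAU sessions are constant at zero, so the session slope is estimated wholly within CR. Apart from covariate adjustment,

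arm coefficient = as-allocated difference − slope × mean CR sessions.

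This is the fitted contrast for a CR participant with no sessions.

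**4. Illustrative simulation.** 175 per arm, 1,000 runs per setting, outcome SD 1 before any treatment effect. The ANCOVA adjusted for a baseline score (coefficient 0.5) but not for the stratification variables. An unmeasured prognostic factor had coefficient 0.4, and ρ is its correlation with the propensity to attend. Sessions out of 14 averaged about 11.9 with SD 2.3, so the results bear on follow-up. The SE of the arm effect rose from 0.093 to about 0.35.

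| | ρ = 0 | ρ = 0.3 | ρ = 0.6 |
|---|---|---|---|
| No true effect: arm coefficient | −0.01 | −0.58 | −1.11 |
| No true effect: session slope significant | 4% | 40% | 92% |
| Constant effect +0.30: arm coefficient | +0.29 | −0.26 | −0.81 |
| Effect proportional to sessions (as-allocated 0.30): arm coefficient | 0.02 | −0.56 | −1.12 |

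Check with the identity in step 3, constant effect and ρ = 0.3: 0.298 − 0.047 × 11.86 = −0.26.

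**5. Sessions replacing arm.** The slope is now identified mainly by the arm contrast. With a constant effect, the per-session benchmark is 0.30/11.9 = 0.025. The slope averaged 0.023, 0.027 and 0.030 at ρ = 0, 0.3 and 0.6. Under no effect it was significant in 6%, 6% and 14% of runs. The Monte Carlo SE at a 5% rate is √(0.05 × 0.95/1000) = 0.7 points, so only the 14% is clearly inflated.

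**6. Excluding poor attenders.** No calculation is needed: this removes a selected subset of CR and no matching subset of TAU.

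**7. Allocation as instrument.** The per-session estimate averaged 0.025 when an effect was present and 0.000 when it was not, at every ρ.

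**The case against.** The wording does not say how compliance enters the model. Sessions could be added to arm, replace it, or define a minimum, and the separate analysis plan, which is not shown, may settle this. The large numbers in step 4 belong to one reading and to assumed attendance. If attendance is unrelated to prognosis and the effect is constant, the arm coefficient is essentially unbiased (+0.29), only imprecise. The simulation also omits the stratification covariates, which might absorb some of the selection.

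All of this stands as a limit on size. It does not remove the point: the article fixes a repeat of an ANCOVA on allocated group and names no randomisation-based method, and none of the three readings gives a protected effect of treatment received.

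Two stronger readings might be inferred and are not supported:

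- **That arm and sessions are simply aliased.** This is exact only with identical attendance throughout CR.
- **That session counts unblind the analysts.** The article says "The code will be broken only after the primary analysis has been completed" and confines compliance to secondary analyses. Nothing in it releases the counts before the primary analysis.

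**Conclusion.** The point holds as a moderate one. As described, analysis 3 does not estimate an effect of treatment received that randomisation protects. The loss of precision when sessions are added to arm is arithmetic once the attendance distribution is given: the VIF is about 85 to 4 over the assumed range. The direction and size of bias depend on how attendance relates to prognosis, which the article does not quantify, so the simulated values are illustrative only.

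A reader might infer that the trial's conclusion is in danger. The document does not support that. The principal analysis is treatment-as-allocated for primary and secondary outcomes, compliance is kept to secondary analyses, and the sample size stands.

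**What to change.** Replace analysis 3 with a complier-average causal effect analysis by two-stage least squares:

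- allocation as the instrument;
- sessions completed before the assessment in question as the exposure (up to 10 at post-intervention, up to 14 at follow-up);
- the same baseline and stratification covariates as analysis 2.

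Report the per-session effect as the main form. Keep any minimum-sessions version as a sensitivity analysis, because it additionally assumes no benefit below the threshold.

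State the assumptions. The exclusion restriction says that allocation affects outcome only through sessions. It deserves explicit discussion here, because participants know their allocation and rate their own goal performance. The per-session form also assumes linearity.

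The cost is a change of wording and standard software, with no new data and no change in sample size. The interval will be wider than that of the as-allocated effect on the corresponding scale.

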### Sample size

Power calculations and attrition rates are based on findings from the pilot trial. We wish to confirm the finding that the primary effectiveness outcome of goal performance was improved in the treatment group
[45]. The difference observed in the pilot was large (standardised effect >1 at post-intervention assessment). However, we also wish to detect any effect sizes in the order of 0.3 for important secondary outcomes, as we judge that this will give confirmation of effects that are large enough to have substantive clinical benefits. For the present study, intervention length has been increased and now includes a maintenance phase in order to further strengthen demonstrable effect sizes in secondary outcomes. We have elected to be conservative in all aspects of our estimate of power, and we have made a larger estimation of potential attrition than the <20% observed in that study, based on the 27% rate observed in the recent REMCARE trial
[59]. To achieve 80% power to detect a medium effect size of 0.3, with alpha 0.05, in primary and secondary outcomes, 175 PwD, with their carers, need to complete the trial in each arm. Adjusting for potential attrition, we aim to randomise 480 PwD, each with a carer. There will be one practitioner involved at each centre, and we will test for differences between sites in the analysis. If there is a change of practitioner at one or more centres during the course of the trial we will also test for practitioner effects.

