#### (5) Demographic and background information for the person with dementia and carer

Details such as gender, age, relationship between person with dementia and carer and whether they live together, age of onset of dementia, educational level, social class and co-morbidities will be collected. This will allow us to examine effects of demographic and social variables on treatment efficacy.

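### Forward stepping at 5% is an unreliable way to find what modifies the CR effect; pre-specified allocation-by-factor interactions, all reported as exploratory, should replace it

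*Protocol article*

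**What the plan says.** The Statistical analysis section of the protocol article sets out three main analyses for each outcome at each follow-up. It then adds a further step, triggered by "If CR is shown to be effective": "additional forward stepping regression modelling will be undertaken to identify factors important in maximising the observed effects". The candidates are named: "Factors that will be investigated will include diagnostic category, medication status, educational level, social class, caregiver relationship to the person with dementia" and "whether or not the carer is residing with the person with dementia". That makes six factors, in a list worded so that others may be added.

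The same section sets the error level: "Significance will be assumed to be 5% throughout, and 95% confidence intervals will be quoted". It gives no separate entry rule for the stepping and no multiplicity adjustment.

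Outcome measures, item (5), gives the reason for collecting the background variables: "This will allow us to examine effects of demographic and social variables on treatment efficacy".

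The article does not say whether candidates enter as main effects or as allocation-by-factor terms, whether both arms or only the CR arm are modelled, or which outcome is used. It promises an analysis plan before the data are released; that plan is not shown.

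**The concern.** The observed effect is a difference between arms. Asking what makes it larger, or how background variables bear on efficacy, is a question about effect modification, and the quantity that answers it is the allocation-by-factor interaction. The article names a selection algorithm instead and mentions no interaction.

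Two problems follow, of different standing.

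- **On any reading.** Forward stepping searches the candidates and keeps those that pass the threshold. The p-values, coefficients and intervals printed for the survivors take no account of the search. They are too optimistic, and some survivors are chance findings.
- **On one reading.** If candidates enter as main effects, the procedure finds factors that predict outcome in both arms, which is a different question from who gains more from CR.

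At stake is the credibility of any published list of factors said to enhance the CR effect.

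**Working it through.** **1. The plan's own figure.** The Sample size section states: "To achieve 80% power to detect a medium effect size of 0.3, with alpha 0.05, in primary and secondary outcomes, 175 PwD" (per arm), with attrition "based on the 27% rate observed in the recent REMCARE trial" and 480 to be randomised.

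- n per arm = 2(1.960 + 0.842)²/0.3² = 174.4, rounded up to 175. Power at 175 per arm is 0.801.
- 350/(1 − 0.27) = 479.5, rounded up to 480.

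Both figures reproduce. The checks below use N = 350 completers, 1:1 allocation, SD 1 and two-sided 5%. Sidedness and the 5% entry level are assumptions; the latter is taken from the article's general significance level.

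**2. Chance of at least one false factor.** With six independent tests and no true effect: 1 − 0.95⁶ = 0.265. If each of the two factors with three categories (diagnosis and carer relationship) were entered as two separate comparisons, there would be eight tests and 1 − 0.95⁸ = 0.337. Separate levels are not strictly independent, so this is approximate. Correlation between factors, plausible for carer relationship and co-residence, would lower the figure. Additions to the open list would raise it.

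**3. Forward selection simulated.** There were 1,500 runs per scenario, entry at p<0.05, a 0.3 SD CR effect and six factors, with multi-level factors entered jointly. Assumed category shares:

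- diagnosis and carer relationship: 70/20/10
- medication: 30/70
- education and social class: 40/35/25
- co-residence: 50/50

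The prognostic factor shifts the outcome by 0.5 SD in both arms for one education level (25% of participants) and modifies nothing. The modifier changes the CR effect by 0.6 SD between co-residence groups, with no average main effect.

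| Candidates enter as | Any factor selected, nothing true | Prognostic factor selected | True modifier selected |
|---|---|---|---|
| Main effects, both arms | 24.5% | 95% | 4% |
| Main effects, CR arm only | 26.4% | 71% | 51% |
| Allocation-by-factor terms | 26.6% | 4.5% | 79% |

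The first column barely moves: the chance-finding problem does not depend on the model form. The other two columns depend on it almost entirely.

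**4. Power for one interaction.** For a two-level factor with share p in one level, SE = √(4/(Np) + 4/(N(1 − p))).

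- p = 0.5: SE = √(4/175 + 4/175) = 0.214. Power for 0.3 SD = Φ(0.3/0.214 − 1.96) = 0.29. Detectable at 80% power: 2.80 × 0.214 = 0.60 SD.
- p = 0.2: SE = √(4/70 + 4/280) = 0.267. Power for 0.3 SD = 0.20. Detectable at 80% power: 2.80 × 0.267 = 0.75 SD.

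The detectable interaction is therefore 2 to 2.5 times the 0.3 SD design effect. The 0.3 SD interaction is a benchmark borrowed from that design effect; the article gives no expected interaction.

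**5. Bias after selection.** At an even split, an interaction passes the 5% threshold only if its estimate exceeds 1.96 × 0.214 = 0.42 SD in size. If the truth is 0.3 SD, every selected estimate in the right direction overstates it, by at least 0.42/0.30 = 1.4 times. At 20/80 the threshold is 1.96 × 0.267 = 0.52 SD.

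**The case against.** **The model form is undefined, not wrong.** The stated aims fit interaction candidates at least as well as main effects, and an analysis plan not shown may specify them. This stands. A reader might infer that the procedure picks prognostic factors and not effect modifiers, so that its conclusions must be wrong. The document does not support that: it holds for main-effect entry, partly for modelling the CR arm alone, and not for interaction candidates, where a purely prognostic factor is selected in about 5% of runs.

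**The detail belongs to the analysis plan.** This stands for entry rule, outcome and coding. It does not cover forward stepping itself, which the article states. A plan that follows the article would still select on the data.

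**The alternative shares the weaknesses.** Six interaction tests at 5% carry the same chance of a false positive, about 26%, and the same low power. This stands. The gain is that all six estimates are reported unselected, so each interval has its usual meaning and none is inflated by selection.

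**The analysis is additional and conditional.** This stands. Looking for what enhances an effect only once one has been shown is a defensible choice, not an error. A reader might also infer that the output will decide who is offered CR in practice. The article discusses bringing CR into routine care in general terms and ties no such decision to these factors.

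**Conclusion.** The concern holds in a limited form. The article fixes data-driven selection at 5% for an effect-modification question and names no interaction term. Whatever terms enter, the reported p-values, coefficients and intervals would be unreliable, with about a 26% chance of at least one false factor per outcome and time point. That figure assumes six independent candidates, one test each and entry at 5%. Selecting prognostic factors in place of modifiers is a further risk that depends on main-effect entry, which is not stated.

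Power for a modest interaction is low under any method: 29% at an even split and 20% at 20/80 for 0.3 SD, assuming a two-level factor, 350 completers and SD 1. Larger modification is conceivable on the primary outcome, where the pilot's standardised effect exceeded 1; for 0.6 SD, power is 80% at an even split and 61% at 20/80.

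The primary comparison and the sample size are untouched.

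**What to change.** Replace the forward stepping with the following.

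- For each of the six listed factors, fit one pre-specified allocation-by-factor interaction, added singly (with the factor's main effect) to the adjusted analysis of covariance. Use a joint test for any factor with more than two levels.
- Name the outcome and time point to which this applies.
- Report all six sets of interaction estimates with 95% confidence intervals, without selection, labelled exploratory.
- State the low power alongside, and that no factor will be declared a modifier on p<0.05 alone.

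Reporting the interactions when CR is not effective overall is optional.

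The cost is a change of wording and no new data; the analysis becomes simpler. The downside is small: there will be no single list of best predictors, and the roughly 26% chance of at least one nominally significant interaction remains.
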